4.12.1 DATA AND STATISTICAL ANALYSIS

Statistical Packages for Social Sciences (SPSS) version 25 would be employed in the analysis of results. Charts and tables would be used to represent collected data. Means and standard deviations will be used to represent continuous data. T-test would aid the assessment of parametric variables and Mann Whitney U-test would be used for non-parametric ones. Statistical test of significance would be deduced at p-value less 0.05.

DUMMY TABLE 1 SOCIO-DEMOGRAPHIC AND CLINICAL CHARACTERISTICS OF THE STUDY POPULATION

| CHARACTERISTIC | ALL | GEL GROUP | NON GEL- GROUP | P-VALUE |
| --- | --- | --- | --- | --- |
| AGE: (years)  25-30  31-40  41-50  Above 50 |  |  |  |  |
| PARITY:  P0  P1  P2-4  P>5 |  |  |  |  |
| MARITAL STATUS  Single  Married  Divorced  Widowed |  |  |  |  |
| MENOPAUSAL STATUS:  Pre-menopausal  Post-menopausal |  |  |  |  |
| USE OF HORMONAL DRUGS OR DEVICES:  Positive history  Negative history |  |  |  |  |

TABLE 2. PAP SMEAR SAMPLE ADEQUACY

| **Laboratory Findings** | **All** | **Gel** | **No gel** | **P-value** |
| --- | --- | --- | --- | --- |
| Satisfactory Pap smear sample |  |  |  |  |
| Unsatisfactory Pap smear sample |  |  |  |  |

TABLE 3. PAP SMEAR RESULT PATTERNS

| Pap smear results | All | Gel | No gel |
| --- | --- | --- | --- |
| HSIL |  |  |  |
| LSIL |  |  |  |
| ASC-US |  |  |  |
| ASC –H |  |  |  |
| BCC |  |  |  |
| WITHIN NORMAL LIMITS |  |  |  |

**List of abbreviations:** HSIL-High Grade Squamous Intraepithelial Lesion, LSIL- Low Grade Squamous Intraepithelial Lesion, ASC-US- Atypical Squamous Cells of Undetermined Significance. ASC-H- Atypical Squamous Cells in which a High-Grade Squamous Intraepithelial Lesion (HSIL) cannot be excluded, BCC-Benign Cellular Changes.

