**2**.**4 Speculum lubrication and adequacy of cervical smears**

The practice of speculum lubrication for vaginal examination is varied due to the fears that lubricants can alter the adequacy of cytological smears. However, recent studies have investigated the relationship between speculum lubrication and Pap smear accuracy and showed evidence supporting that speculum lubrication does not disrupt the evaluation of cytological smears.

Amies et al^33^ in their study randomized five public health family planning clinics in USA to lubricating gel and water arms. A sum of 2906 Pap smear specimens were obtained, 1440 from units using lubricants and 1466 from the non-lubricant using clinics. A dime size of the lubrication gel was stated to have been applied on the external part of the inferior blade of the plastic disposable speculum which is not objective as this might be difficult to ascertain by different people because a dime is not a standard way of measurement. Inadequate smear rate for the clinics using lubricant compared to clinics not using lubricants was 1.4% versus 1.3%. The percentage of inadequate smears for the clinics using gel did not differ significantly from those of the control clinics [Odds ratio (OR) 1.1; 95% Confidence Interval (CI) 0.6, 2.0]. Reasons for unsatisfactory smears were scanty cells, excess blood and inflammation. Drying artefact or gel overlay was not encountered as causes of encumbrance in evaluation. They did not evaluate the pain level during speculum insertion.^33^

In 2012, Uygur et al ^20^ demonstrated in Turkey that speculum lubrication did not alter cervical cytological smears. A total of 400 eligible women were grouped at random into two arms: the gel and no gel groups. Each arm was then subsequently randomly divided to have liquid based smears or conventional smears. Dime sized gel was spread on the outer side of the lower blade as done by Amies et al which is not a standard way of measurement and will not be easily reproducible. Out of the 400 women only 3 unsatisfactory results were recorded, one from the group that did not use gel( 0.5%) and two from the other group(1%).^20^

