**3.2 SPECIFIC OBJECTIVES**

1. To compare the pain experienced by women undergoing cervical cancer screening with speculum lubrication and those without speculum lubrication.

2. To compare the proportion of unsatisfactory cytology smear results of women undergoing cervical cancer screening with speculum lubrication and those without speculum lubrication.

3. To compare the proportion of women willing to come for repeat cervical smears in the future

after undergoing initial cervical cancer screening with speculum lubrication and without speculum lubrication.

3.3 **RESEARCH QUESTIONS**

1. Does speculum lubrication affect the comfort of women undergoing cervical cancer screening using Pap smear?

2. Does speculum lubrication affect the adequacy of cytology results of women undergoing cervical cancer screening using Pap smear?

3.**4 Null hypothesis**

1. Speculum lubrication does not significantly affect the comfort of women undergoing cervical cancer screening using Pap smear.

2. Speculum lubrication does not significantly affect the adequacy of cytology smears of women undergoing cervical cancer screening using Pap smear.

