**3.5 Alternative hypothesis**

1. Speculum lubrication significantly affects the comfort of women undergoing cervical screening using Pap smear.

2. Speculum lubrication significantly affects adequacy of cytology smears of women undergoing cervical screening using Pap smear.

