**CHAPTER FOUR**

**RESEARCH METHODOLOGY**

4.**1 STUDY DESIGN**

The work will be a randomized controlled study.

4.2 **STUDY SETTING**

This work will be done in the gynaecology clinic of Nnamdi Azikiwe University Teaching Hospital (NAUTH) Nnewi, Anambra State Nigeria. NAUTH is the only federal teaching hospital in Anambra State, a state in the South eastern part of the country. It offers comprehensive and tertiary services to occupants of Anambra, Enugu, Delta, Imo and Abia states. It is structured to offer medical undergraduate and medical postgraduate training as well as paramedical training. It is also well grounded in medical research. This teaching hospital is well equipped to offer obstetric, gynaecological and gynae-oncology services both on in-patient and outpatient bases. Nnewi is one of the biggest towns in Anambra state and consists of 4 villages which include Nnewichi, Uruagu, Umudim, and Otolo. ^41^ It is a place known for its industrial and commercial activities. It is home to the popular Nkwo Nnewi market, the biggest market for motorcycle spare parts in West Africa.^41^ It is home also to major automobile, petrochemical and cosmetic industries and the first indigenous car producing plant in Nigeria. The inhabitants are mainly Christians who speak Igbo majorly and are mostly traders.

4.**3 SAMPLE SIZE DETERMINATIONf**

The sample size will be calculated using the formula for sample size Determination of minimum sample size for experiemtal studies (Difference in proportions) ^42^ substituting for the values of proportion of unsatisfactory smears as found in a previous study ^20^

n **=** [(Z**_β_** + Z**_α/2_**)^2^ x 2P(1−P)] **=** Minimum sample size

E ^2^

Where

P **=** (P_1_ + P_2_) / 2 **=** (0.01+ 0.005) / 2 **=** 0.0075

E **=** Effect size **=** P_1_ - P_2_ **=** 0.01- 0.005 **=** 0.005

Z**_β_ =** Corresponding Z value at 80% Power **=** 0.84

Z**_α/2_** **=** Corresponding Z value at 95% confidence level **=** 1.96

n **=** [(0.84 + 1.96)^2^ x 2(0.0075)(0.9925)] **=** 0.116718 **=** 4668.72 **≈** 4669

(0.005) ^2^  (0.005) ^2^

Adjusting for finite population, N = 60 samples from clinic in 3 months.

n_s_ **=** n^1^ / 1 + n^1^/N

Where;

n_s_ **=** Adjusted sample size

n^1^ **=** Calculated sample size

N **=** population for study

n_s_ **=** 4669 / (1 + 4669/60) = 4669/78.82 = 59.2 **≈** 60

This will be approximately 60 making a total of 120 with 60 controls and the other 60 for intervention arm.

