The vial will then be taken to the histopathology laboratory of Nnamdi Azikiwe University Teaching Hospital, Nnewi where it would be transferred into a centrifuge tube with same quantity of cleaning solution. The fluid will then be centrifuged for 10 minutes at 1400 rpm; the supernatant will be removed. Smears will be made from the sediments after mixing with the cellular base solution (Diapath S.p.A Martinego, Italy) and stained by the Papanicolaou staining method and reported using the Bethesda system stating whether the sample is satisfactory or not and the reason for unsatisfactory results. Samples will be recorded as “unsatisfactory” if no endocervical cells are present, if they are obscured by blood, or if drying artifact or gel overlay are present; otherwise, they will be recorded as “satisfactory”. ^19^ The histopathologist will not be aware of the intervention arm (group of patients) to which the smears to be analysed belong.

4.11 **OUTCOME MEASURES**

The primary outcome measures will be the mean NRS pain scores and proportion of women with inadequate cervical cytology smears while the secondary outcome measures will be the pattern of Pap smear results and proportion of women willing to come for repeat testing.

4.12 **PLANNED HANDLING OF RESULTS**

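### Smear adequacy is decided by a p < 0.05 difference test with no margin, so a near-certain non-significant result could pass for evidence that gel does no harm

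*Protocol*

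**What the plan says.** Section 4.11 of the protocol gives two primary outcomes: "The primary outcome measures will be the mean NRS pain scores and proportion of women with inadequate cervical cytology smears".

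The introduction explains why adequacy matters: trainees are advised against lubricating the speculum because gel may interfere with the cytology. The concern is therefore harm in one direction.

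The hypotheses are framed differently. The null in section 3.4 is "Speculum lubrication does not significantly affect the adequacy of cytology smears of women undergoing cervical cancer screening using Pap smear", and the alternative in section 3.5 is "Speculum lubrication significantly affects adequacy of cytology smears of women undergoing cervical screening using Pap smear". Neither names a margin.

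On analysis, section 4.12.1 says "T-test would aid the assessment of parametric variables and Mann Whitney U-test would be used for non-parametric ones", and "Statistical test of significance would be deduced at p-value less 0.05". Dummy Table 2 counts satisfactory and unsatisfactory samples by arm, with a p-value column and no column for a difference or an interval.

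Section 4.3 plans on unsatisfactory rates of 1% with gel and 0.5% without, taken from a cited trial in which two and one smears were unsatisfactory among 400 women. It calculates 4669 and reduces this to about 60 per arm by a finite-population adjustment. Adding 10% for attrition gives 66 per arm, 132 in all.

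**The concern.** A test of no difference can show that gel affects adequacy. It cannot show that gel leaves adequacy intact. That needs an interval narrow enough to exclude a difference that would matter, and so a margin.

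The null in section 3.4 is also worded as a statement about significance rather than about the true rates. If p is 0.05 or more, the retained hypothesis reads as a finding of no effect. The literature review already moves this way: in section 2.4 it passes from rates that did not differ significantly to the conclusion that lubrication leaves smear quality unaffected.

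At stake is one of the trial's two main questions. A statement that gel is safe for cytology could influence screening practice, although data of this size would be compatible with a rise of several percentage points in unusable smears.

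**Working it through.** **Inputs.** Rates of 1% and 0.5%, Z values of 0.84 and 1.96, N = 60, and 60 or 66 per arm (section 4.3); criterion p < 0.05 (section 4.12.1), two-sided because section 4.3 uses Z at α/2; the harm scenario of 12.1% v 1.7% (section 2.4, a study that put gel on the cervix). The 5% and 15% gel rates below are assumed for illustration.

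**1. The plan's own figure.**
- n = (0.84 + 1.96)² × 2 × 0.0075 × 0.9925 / 0.005² = 4668.72, so 4669. This reproduces.
- 4669 / (1 + 4669/60) = 59.2, taken as 60; 60 + 6 = 66. This also reproduces.
- The formula's 80% power belongs to 4669 per arm, not to 60.

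**2. Events expected at the planning rates.**
- 60 × 0.01 + 60 × 0.005 = 0.9 unsatisfactory smears in the whole trial; at 66 per arm, 0.99.
- Chance of none in either arm: 0.99⁶⁰ × 0.995⁶⁰ = 0.41; at 66 per arm, 0.37.

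**3. What it takes to reach p < 0.05 by Fisher's exact test, 60 per arm.** With k events against 0, and k small, the two-sided p is 2 × C(60,k) / C(120,k).
- 5 v 0: p = 0.057.
- 6 v 0 (10% v 0%): p = 0.027.

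**4. Exact power.** This is the sum, over all pairs of counts with p < 0.05, of the product of the two binomial probabilities.

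| True rates, gel v no gel | Fisher, 60 per arm | Uncorrected chi-square, 60 | Fisher, 66 | Chi-square, 66 |
|---|---|---|---|---|
| 1% v 0.5% | 0.002% | 0.24% | 0.004% | 0.33% |
| 5% v 0.5% | 6% | 27% | 8% | 31% |
| 12.1% v 1.7% | 47% | 66% | 54% | 71% |
| 15% v 0.5% | 84% | 94% | 89% | 96% |

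In the first row a non-significant result is at least 99.6% likely with either test. The usual normal approximation gives 5.0% power at 60 per arm and 5.2% at 66, but it is unreliable with about one event expected.

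**5. What an interval would show.** Newcombe 95% upper limit for gel minus no gel: d + √[(u₁ − p₁)² + (p₂ − l₂)²], where d = p₁ − p₂, u₁ is the Wilson upper limit for gel and l₂ is the Wilson lower limit for no gel.
- 0 v 0 at 60 per arm: u₁ = 6.0%, so the limit is 0 + √(6.0² + 0²) = +6.0 points; at 66 per arm, +5.5.
- 1 v 0: +8.9 points; at 66 per arm, +8.1.
- 2 v 1: +9.8 points; at 66 per arm, +9.0.

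Each limit is many times the 0.5-point difference on which section 4.3 plans.

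**The case against.** Several points on the other side have force.

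- **A reader might infer that the plan applies the t-test or Mann-Whitney test to the adequacy proportion.** The text does not support this. Section 4.12.1 names those tests without assigning either to Table 2, and an SAP could name a categorical test. The missing name is not the defect. Naming Fisher's test would leave the hypothesis, criterion and size as they are.
- **A reader might infer that p ≥ 0.05 is guaranteed whatever gel does.** That goes too far. At 15% v 0.5% Fisher power is 84% with 60 per arm, so very large harm would probably be detected.
- **A reader might take +6 points as a floor for the upper limit.** It is only the 0 v 0 result at 60 per arm. With no events on gel and one in controls the limit is +4.5, and at 66 per arm 0 v 0 gives +5.5.
- **The planning rates may not apply here.** Section 4.10 counts a smear without endocervical cells as unsatisfactory, and whether the source trial did so cannot be seen. A higher rate would not rescue the test: at an assumed 20% v 10%, power with 60 per arm is 25% (Fisher) or 33% (chi-square).
- **No sentence says that a non-significant result will be reported as no effect.** True. This is inferred from the wording of the null, the layout of Table 2 and the way the literature review reads such results. The limitations in section 4.13 do not warn against it.
- **A difference hypothesis is a legitimate design, and the power was lost in the sample-size step.** Both are fair. The finite-population cut is a separate matter. The point here is what may be concluded at the size planned.

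**Conclusion.** The point holds as one about the hypothesis, the decision criterion and the reading of the result. Adequacy is co-primary and its concern is harm, yet it is framed as a difference test at p < 0.05 with no margin and a table that shows only a p-value. If the planning rates of 1% and 0.5% apply, a non-significant result is over 99% likely at 60 to 66 per arm by exact calculation. A tenfold rise to 5% would be missed about 94% of the time by Fisher's test at 60 per arm, and 12.1% v 1.7% about 53% of the time. Following the plan as written would almost surely retain a null that reads as no effect, on data that could not support it.

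The size of the problem depends on the true rates and on the test: it is near-certain for small differences and fades for very large ones. The predicted misreading is an inference from the wording, not a stated intention.

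**What to change.** In sections 3.4, 3.5 and 4.12.1 and in Table 2:

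- Make the risk difference (gel minus no gel) with a 95% score or exact interval the main adequacy result, and use an exact test for any p-value.
- State that p ≥ 0.05 will not be read as showing that gel does not affect adequacy.
- Allow that conclusion only if the upper limit lies below a margin fixed in advance and justified; otherwise report the result as inconclusive. The documents give no margin, so the investigators must choose one.
- Give the precision to expect as an illustration, not as a bound: 0 v 0 gives a Newcombe upper limit of about +6.0 points at 60 per arm (+5.5 at 66), and 1 v 0 gives +8.9 (+8.1).

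The cost is wording and one extra column in Table 2; no more women are needed. The downside is real: the permitted adequacy conclusion is weaker and, at this size, will probably be inconclusive.

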**TABLE 4: WILLINGNESS TO COME FOR REPEAT TESTING**

| Willingness to come for repeat testing | ALL | GEL | NO GEL | P VALUE |
| --- | --- | --- | --- | --- |
| YES |  |  |  |  |
| NO |  |  |  |  |

FIGURE 1. NUMERICAL RATING SCALE FOR PAIN

4.13 **STRENGTH AND LIMITATIONS OF THE STUDY**

This study is the first of its kind in a low income country like Nigeria, The limitation is that only one type of water- based lubricant will be used so results may not be applied to other kinds of lubricants. Perception of pain is complex and multifactorial. Cultural and genetic factors can affect these results in different populations.

Pap smear collection is provider technique dependent. Even though the researcher and research assistants will all be senior resident doctors with same level of training and experience, there still may be chances of inter provider differences. Except for the histopathologist, the researcher, research assistants and patients will be aware of the intervention assignment because given the nature of the intervention technique, blinding of participants and researcher/ research assistants will be difficult.

**4.14 CONFLICT OF INTEREST**

There would be no conflict of interests.

**APPENDIX 2**

**RESEARCH PROFORMA**

**EFFECTS OF SPECULUM LUBRICATION ON CERVICAL SMEARS FOR CERVICAL CANCER SCREENING: A DOUBLE-BLIND RANDOMIZED CONTROLLED TRIAL**

Please do fill the parameters below. Tick [X] where appropriate.

Code No………Folder Number………………Date of Enrolment……………

**PARTICIPANT INFORMATION SECTION**

1. **ELIGIBILITY CHECK LIST**: A subject is not eligible if the answer to any of these is YES
2. Menstruating YES [ ] NO [ ]
3. Pregnant YES [ ] NO[ ]
4. Cervical cancer patient YES [ ] NO [ ]
5. Vulvar lesion or malignancy YES [ ] NO[ ]
6. History of cervical or vulvar surgeries YES [ ] NO[ ]
7. Hormone therapy YES [ ] NO[ ]
8. Vaginitis YES [ ] NO[ ]

1. **BIODATA**
2. **AGE AS AT LAST BIRTHDAY(YEARS)…**……25-30 [ ] 31-40 [ ] 41-50 [ ] >50 [ ]
3. **PARITY**:

P0 [ ] P1 [ ] P2 [ ] P3 [ ] P4 [ ] P5 [ ] P>5 [ ]

1. **MARITAL STATUS:**

SINGLE [ ] MARRIED [ ] DIVORCED/SEPARATED [ ] WIDOWED [ ]

1. **EDUCATIONAL STATUS:**

NO EDUCATION [ ] PRIMARY [ ] SECONDARY [ ] TERTIARY [ ]

1. **RELIGION:**

CHRISTIANITY [ ] ISLAM [ ] TRADITIONAL [ ]

1. **OCCUPATION………………………………………**
2. **ETHNICITY**

IGBO [ ] HAUSA [ ] YORUBA [ ] OTHERS Specify……

1. **SMEAR SAMPLE STATUS**

SATISFACTORY [ ] UNSATISFACTORY [ ]

UNSATISFACTORY( SPECIFY REASON)………………

1. **PAP SMEAR RESULT**

HSIL [ ] LSIL [ ] ASCUS [ ] ASC-H[ ] BCC [ ] NORMAL LIMIT[ ] INFECTION/CERVICITIS [ ]

1. **NUMERIC RATING SCALE-** what number best describes your pain during the procedure

**0 [ ] 1[ ]2 [ ] 3 [ ]4[ ]5 [ ] 6 [ ]7 [ ] 8 [ ] 9[ ]10 [ ]**

**(where 0 is No pain and 10 worst possible pain)**

1. **SATISFIED WITH PAP SMEAR PROCEDURE**

YES [ ] NO [ ]

1. **ARE YOU WILLING TO COME FOR REPEAT TESTING IN THE FUTURE**

YES [ ] NO [ ]

If no give reasons……………………………………………………………………..

